### 3. STUDY DESIGN

This study is a multicenter randomized intra-patient controlled trial conducted in the burn centers of the Red Cross Hospital Beverwijk in the Netherlands and of the University Hospital Ghent in Belgium. Inclusion period is three years. Individual patient follow-up is 12 months.

## 4. STUDY POPULATION

### 4.1 Population (base)

All adult patients with (burn) wounds affecting 4 - 20% total body surface area with an indication for surgical excision and skin grafting, admitted to the burncentre at the Red Cross Hospital in Beverwijk in the Netherlands (n=30) or the burncentre of the University Hospital Ghent in Belgium (n=40).

### 4.2 Inclusion criteria

- Patients  $\geq 18$  years
- Clinically deep burn or deep skin defect between 4% and 20% TBSA
- Patients with two comparable deep partial thickness and/or full thickness burns, confirmed by laser Doppler imaging (LDI) or deep skin defects, of minimum 1:2 plissee = 36cm^2, requiring surgery after assessment by a (plastic) surgeon/burn physician
- Patients who are mentally capable to give legal consent or legal representative when the patient is temporarily incompetent (e.g. patient is sedated/ventilated)

### 4.3 Exclusion criteria

- Patient has participated in another study utilizing an investigational drug or device within the previous 30 days
- Wounds covering face, hands or joints
- Patient has one or more medical condition(s) that in the opinion of the treating physician would make the patient an inappropriate candidate for this study
- Patients who are expected (according to the responsible medical doctor) to be non-compliant to the study protocol. (This includes patients with severe cognitive dysfunction/impairment and severe psychiatric disorders).

### 4.4 Sample size calculation

Sample size calculation based on scar quality as expressed by POSAS at 12 months post procedure: Paired t-Test for Mean Difference

| Fixed Scenario Elements |        | Computed N Pairs |               |              |         |
|-------------------------|--------|------------------|---------------|--------------|---------|
| Distribution            | Normal |                  |               |              |         |
| Method                  | Exact  |                  |               |              |         |
| Number of Sides         | 2      |                  |               |              |         |
| Alpha                   | 0.05   |                  |               |              |         |
| Mean Difference         | 1      |                  |               |              |         |
| Standard Deviation      | 2.4    |                  |               |              |         |
| Correlation             | 0.5    |                  |               |              |         |
| Null Difference         | 0      |                  |               |              |         |
|                         |        | Index            | Nominal Power | Actual Power | N Pairs |
|                         |        | 1                | 0.8           | 0.807        | 48      |
|                         |        | 2                | 0.9           | 0.902        | 63      |

For a superiority trial comparing 2 paired means, a sample size of 63 patients yields 90% power when assuming a true mean difference of 1, a standard deviation of 2.4 and a moderate correlation of 0.5. Expecting a drop-out rate of 10% the sample size is increased to 70 patients.

Sample size calculation based on donor site size and expansion rate: Paired t Test for Mean Difference

| Fixed Scenario Elements    |           | Computed N Pairs |        |        |       |                     |
|----------------------------|-----------|------------------|--------|--------|-------|---------------------|
| Distribution               | lognormal | Geo              | Geo    | Actual | N     |                     |
| Method                     | Exact     | Index            | Mean 1 | Mean 2 | Power | Pairs               |
| Number of Sides            | 2         |                  |        |        |       |                     |
| Alpha                      | 0.05      |                  |        |        |       |                     |
| Coefficient of Variation 1 | 0.09      | 1                | 1      | 1.1    | 0.914 | 13 (10% difference) |
| Coefficient of Variation 2 | 0.03      | 2                | 1      | 1.2    | 0.960 | 6 (20% difference)  |
| Correlation                | 0         |                  |        |        |       |                     |
| Nominal power              | 0.9       |                  |        |        |       |                     |
| Null Geometric Mean Ratio  | 1         |                  |        |        |       |                     |

For a paired t test of a lognormal geometric mean ratio with a two-sided significance level of 5%, assuming coefficients of variation of 0.09 and 0.03 (based on Kamolz et al. 2013) and correlation 0 (to be conservative), a sample size of 6 pairs is required to obtain a power of at least 90% to detect a geometric mean ratio of 1.20. (The actual power is 96%.) This number has been increased to 7 patients to allow for a 10% drop-out rate.

Conclusion of sample size calculations:

Taking into account a drop-out rate of 10%, 70 patients will be required to perform this study.

## **5. TREATMENT OF SUBJECTS**

### **5.1 Investigational treatment**

Prior to the first operation the deep/subdermal wounds will be treated according to the local protocol of the burn centre. Subsequently, surgeons will assess if the wound bed is suitable to receive autografts, possibly after additional debridement. When the wounds are eligible for skin grafting, the two wound areas will be defined. Woundswabs and digital photographs will be taken. Randomization will take place before the first surgery and wound areas will be assigned to either micrografting or meshed grafting. For both techniques an expansion rate of 1:2 will be used for a wounds with 4-10% TBSA and 1:3 for wounds with 11-20% TBSA. Donorsite size will be expressed in cm^2 and objectively measured with a 3D camera (Woundworks inSight®). After operation on day 8 +/- 2 days take rate of both micro- and meshed grafts, will be assessed in expressed in percentage of the harvested skin graft.

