**Study population:** All adult patients with (burn) wounds affecting 4 - 20% total body surface area with an indication for surgical excision and skin grafting, admitted to the burn center at the Red Cross Hospital in Beverwijk, Netherlands or the burn center of the University Hospital Ghent, Belgium.

**Intervention:** Prior to surgery two comparable (burn) wounds or two equal parts in one (burn) with a minimum size of 36 cm^2 will be selected. These wounds will be randomly allocated to the intervention group (micrografting) or the comparison group (meshed skin grafting).

**Main study parameters/endpoints:** The main study parameter is scar quality 12 months after either skin grafting. Possible differences in scar quality between both techniques observed by means of Patient and Observer Scar Assessment Scale (POSAS).

**Nature and extent of the burden and risks associated with participation, benefit and group relatedness:** All patients will have to undergo surgery, independent of skin grafting method. Seen both skin grafting techniques are already been considered as standard treatments, there is no additional risk micrografting compared to meshed skin grafting. The only risk concerns a possible subtle asymmetry of the scar due to two different grafting techniques. However, in practice both techniques are also being combined within one patient. Follow-up broadly corresponds with standard follow-up for (burn) wounds. The duration of check-up at outpatient clinic is slightly increased to 60 minutes, due to additional examinations and surveys.

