## 8.2 Randomisation, blinding and treatment allocation

Randomization will be at intra-patient level and performed by means of the Redcap randomization module (most often 5-7 days post allograft application). Preferably 2 wounds in the same patient will be randomized, or alternatively, after discussing this situation with the patient, 1 wound will be divided into 2 halves (A and B). The sequence in which the micrografting and mesh grafting techniques will be applied will also be subject to randomization by means of the Redcap randomization module. In surgical treatment blinding is not possible, as the burn surgeon knows which part of the wound receives what surgical treatment. Outcome assessment will be blinded as the junior investigator/research nurse who does the follow-up measurements is unaware of the technique used in target wound A or B.

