#### Per-operatively

- Prior to skin grafting debridement(s) and/or allograft applications are performed to prepare wound beds for skin grafting.
- Target wounds will be marked with part A or B with a minimum of 36 cm^2 per wound.
- Digital photographs will be taken of the target wounds.
- Wound swabs for microbiological analysis will be harvested from the wound bed of each target wound before cleaning the wound.
- Randomisation will follow and target wounds will be grafted with the micrografting .technique and the meshed graft technique. Skin grafting techniques are further explained

below (8.3 skin grafting techniques).

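### Section 5.1 times randomisation before an undefined first surgery, against 8.2 and 8.3, so allocation may be known to the unblinded surgeon while the wound beds are being prepared

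*Protocol*

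**What the plan says.** The protocol describes the timing of randomisation in three places.

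- **Section 5.1:** "Randomization will take place before the first surgery and wound areas will be assigned to either micrografting or meshed grafting". Earlier in the same paragraph, "surgeons will assess if the wound bed is suitable to receive autografts, possibly after additional debridement", and then "When the wounds are eligible for skin grafting, the two wound areas will be defined".
- **Section 8.2:** randomisation is within the patient and "performed by means of the Redcap randomization module (most often 5-7 days post allograft application"). The order in which the two techniques are applied is randomised as well. The surgeon cannot be blinded; the person taking the follow-up measurements is.
- **Section 8.3, Per-operatively:** the list opens with "Prior to skin grafting debridement(s) and/or allograft applications are performed to prepare wound beds for skin grafting". Next, "Target wounds will be marked with part A or B", followed by photographs and swabs. Only then: "Randomisation will follow and target wounds will be grafted with the micrografting" and meshed techniques.

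Two other places bear on the order of events. The Summary (Intervention) has the wounds chosen first, "Prior to surgery two comparable (burn) wounds or two equal parts in one (burn"), and then allocated. Section 8.3, Skin grafting techniques, makes debridement the opening step of micrografting and says that debridement for meshed grafting follows a similar procedure.

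**The concern.** In this trial the patient is the block and the two wound areas are the units compared. The comparison is fair if the areas are alike in everything except the grafting technique. Randomisation secures that only if both areas are chosen and prepared before anyone who prepares them knows which technique each will receive.

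The surgeon is unblinded by design, and the stated hypothesis in section 1 is that micrografting gives the better scar. If allocation is known earlier, depth of excision, thoroughness of debridement or use of allograft could differ between the areas, with or without intent. Pairing removes differences between patients, not a difference in preparation within a patient. Blinding the assessor protects the measurement and not what was done to the wound a year before.

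There are two centres, and section 12.2 foresees no monitoring. One centre could work from 5.1 and the other from 8.3, and nothing in the protocol would bring that to light.

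**Working it through.** No arithmetic applies. The check sets the statements side by side and asks which can hold for the same patient.

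| Place | Time of randomisation | What is stated to come first |
|---|---|---|
| Summary | Not given beyond following wound selection | Selection of the two wounds or halves, before surgery |
| 5.1 | Before the first surgery | In text order: suitability assessment, possible further debridement, definition of the two areas, swabs, photographs |
| 8.2 | Most often 5-7 days after allograft | An allograft application |
| 8.3, Per-operatively | During the operation | Debridement and/or allograft, marking of A and B, photographs, swabs |
| 8.3, Skin grafting techniques | Not mentioned | Debridement is itself the opening step of the grafting procedure |

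**8.2 against 8.3.** An autografting operation 5-7 days after the allograft, with randomisation in theatre, satisfies both. There is no conflict.

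**5.1 against 8.2.** A patient randomised 5-7 days after an allograft has already had that procedure. If the allograft operation counts as surgery, randomisation was not before the first surgery. By the wording of 8.2 this is the usual patient.

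**5.1 against 8.3.** Suppose first surgery means the first autografting operation. Section 5.1 is then before that operation and 8.3 is within it, after preparation and marking. The two still differ. The same holds for a patient debrided and autografted in one session.

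**So there are two positions:** before the first surgery (5.1), or at the autografting operation after the wound bed has been prepared (8.2 and 8.3).

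**What is done with the allocation known?**

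- Under literal 5.1: any debridement or allografting in the first and later operations.
- Under 5.1 with first surgery read as autografting: the debridement that opens the grafting procedure.
- Under 8.3: preparation is listed before randomisation, but the technique descriptions start again with debridement, and no sentence says this must be finished in both areas before the allocation is released.

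**Areas A and B.** The Summary, 5.1 and 8.3 each put selection, definition or marking of the areas ahead of allocation. On this point they agree.

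**The case against.** The best defence is that 5.1 should be read as a whole paragraph. It puts assessment of the bed, any additional debridement and definition of the areas before its randomisation sentence. That is close to the order in 8.3, and first surgery may simply mean the first autograft. On this view the defect is a loose phrase, not a decision to allocate early.

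Much of that stands. The protocol does not choose early allocation, so this is an internal inconsistency and not a flawed design choice. It does not dispose of the point. The term is undefined, the paragraph itself opens by speaking of treatment prior to the first operation, and even the lenient reading leaves 5.1 before surgery and 8.3 during it. The debridement that opens each grafting technique remains unplaced under either reading.

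Four stronger inferences are tempting, and the document does not support them.

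- **Three incompatible times.** There are three wordings but two positions, since 8.2 and 8.3 agree.
- **Allocation known while A and B are being fixed.** Every section that gives an order fixes the areas first. The risk arises only by joining the early timing of 5.1 to the per-operative marking of 8.3, a sequence that no section states.
- **Loss of patients after randomisation because a bed proves unsuitable.** Section 5.1 puts the suitability judgement before its randomisation sentence, and no figure ties such losses to the 10% drop-out allowance.
- **A specific inflation of the false-positive rate.** That would need an average one-directional shift in the 12-month score. The protocol gives neither its size nor the share of patients affected, so any rate would only restate the assumption.

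**Conclusion.** The contradiction is real and concerns allocation concealment in the primary comparison. Section 5.1 cannot be reconciled with 8.2 and 8.3 as written, and the protocol does not guarantee that both wound beds are fully prepared before the unblinded surgeon learns the allocation.

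Its effect on the result cannot be quantified from the document. It depends on which section each centre follows and on whether preparation then differs between the areas, and the protocol says nothing on either. The conclusion rests on two readings: that debridement or allografting in theatre counts as surgery, or, failing that, that a time before an operation differs from a time within it. It does not rest on any assumption that surgeons would act on the knowledge; the protocol should exclude the possibility. Timing of randomisation is a trial procedure, so the inconsistency belongs to the protocol and cannot be left to an analysis plan.

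**What to change.** - **5.1:** delete the timing clause that refers to the first surgery.
- **5.1, 8.2 and 8.3:** state one rule, consistent with the Summary. The module releases the allocation and the application order only when debridement of both areas is complete and A and B have been marked, photographed and swabbed. The areas may not be redrawn afterwards. Section 8.2 needs little change; the 5-7 days can stay as a description of when the grafting operation usually falls.
- **8.3, Micrografting and Meshed grafting:** reword so that debridement of both areas precedes release of the allocation. Aligning 5.1 with the per-operative list alone would leave this open.

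The rule governs when the allocation is disclosed, not how or how much the wounds are debrided, and it does not move the time at which swabs are taken.

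The cost is wording in these sections and access to the randomisation module for theatre staff during the grafting operation. No extra patients or measurements are needed.

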### **5.2 Use of co-intervention (if applicable)**

Not applicable

### **5.3 Escape medication (if applicable)**

Not applicable

## 6. INVESTIGATIONAL TREATMENTS

### 6.1 Name and description of investigational treatments

#### Micrografting

Skin transplantation by the micrografting technique was first described in 1958 by Cicero Parker Meek in the USA and therefore also referred as the Meek technique. In 1993 the micrografting technique was modified and re-designed by burn surgeon's in the Red Cross Hospital, Beverwijk in association with Humeca Skin Transplantation Technology, Borne, The Netherlands. After harvesting of the autologous skin grafts, the graft will be displayed on a cork square and will be cut in multiple squares by a specialized micrografting cutting machine. Next, the sliced graft on cork will be sprayed with an adhesive layer and will be placed on a pre-folded gauze. This pre-folded gauze expands when all four sides of the gauze are pulled. Finally, the cork will be removed and the gauze with the graft squares are applied to the wound and fixated with staplers. All pre-folded gauzes will be covered with antibacterial gauzes and thereupon dry sterile gauzes and bandages.

#### Mesh grafting technique

Skin grafts for mesh grafting are harvested by the same method as for the micrografts (see *section 8.3 study procedures for full description of grafting procedures*). After harvesting, the autografts will be displayed over an carrier and pulled through the meshing machine. This cutting machine makes multiple small perforations in the graft, which allows the skin graft to expand. The meshed graft will be attached to the wound and fixated with staplers. Finally, the grafts will be covered with antibacterial gauze and topped with dry sterile gauze and bandages.

### 6.2 Summary of findings from non-clinical studies

Database collected data from the burncentre of the Red Cross Hospital, Beverwijk, show that within 2 years, 134 patients with burn wounds had an indication for skin grafting. In patients with less extensive burns (0-10% TBSA) the majority, 80% (n=77), received meshed skin grafts. Only 20% (n=18) were transplanted with micrografts. In extensive burns (10-20% TBSA) the amount skin grafting procedures with micrografts increased to 55% (n=22). Whereas the number of meshed skin transplantation reduced to 45% (n=17).

### 6.3 Summary of findings from clinical studies

Two studies on micrografting versus mesh grafting for patients with burn wounds have been published:

- Zermani et al. (1997) compared functional and aesthetic results after micrografting and after mesh skin grafting. In this prospective study 5 patients with extensive burns (mean TBSA 35%) were included. Expansion ratio from 1:3 to 1:9 were used for micrografts. 6 months post-surgery functional results were similar for both grafting methods. The aesthetic results were better for micrografts. On long-term both functional and aesthetic results were considered good to excellent in all cases. In

comparison with meshed grafts, micrografts enabled skin grafting with a larger expansion ratio and smaller donorsite size.

- Zhen et al. (2019) examined the long-term functional outcomes of micrografting and split skin grafts (SSG) in burns. It's a cross-sectional setting, including burns of 10-40% TBSA at least one year post-burn. 43 patients were included, micrografting n=15 and SSG n=28. TBSA was significantly higher in the micrografting group, 27% vs. 16% SSG. Functional outcomes were assessed with The Burn Specific Health Score-brief (BSHS-B) and resulted in better scores in micrografting compared with SSG ( $p>0.05$ ). Vancouver Scar Scale (VSS) was used to evaluate scar quality and showed significantly better scar outcomes after micrografting compared to SSG.

One study was published comparing micrografting with non-micrografting procedures:

- Lumenta et al. (2009) is a retrospective study which among others compared micrografting with non-grafting. They analysed burn severity (%TBSA), age, hospital length of stay, amount of operations and mortality for both groups. Patients in the micrograft group were significantly older, had higher % TBSA but had an equal amount of operations and the same length of hospital stay.

Based on abovementioned studies, micrografting seems to show similar or better results compared with mesh skin grafting especially for extensive burn wounds. However, the evidence for these conclusions is very sparse. A randomized controlled trial is needed to adequately compare the micrografting and mesh graft technique for long-term scar quality. Moreover, since donorsite morbidity is a relevant problem in burn surgery, further development of this micrografting technique is also worthwhile for less extensive (burn) wounds.

#### 6.4 Summary of known and potential risks and benefits

Meshed grafts: This technique for skin expansion and grafting is most widely performed, seen it is a very user-friendly and fast procedure. However, mesh grafting also has its shortcomings. Theoretically an expansion ratio from 1:1.5 until 1:9 are possible In practice, meshed grafts do not expand as much as suggested. Expansion ratios of 1:1,5 and 1:3 turned out to give an surface area expansion of 1,36x and 1,80x respectively Moreover, an expansion ratio above 1:3 is very fragile and therefore difficult to properly cover and fixate on wounds. Besides, the 'fish-net' pattern of the meshed graft remains visible in the long-term scar. For this reason, meshed grafts do not fall within the preferred skin expansion and grafting techniques for extensive wounds with limited donorsite.

Micrografting: True expansion ratios up to 1:9 are achieved, which leads to a smaller donorsite. In comparison with meshed grafts, micrografting will not give fragility problems with a large expansion ratio. Also small graft fragment can be used, in contrast with meshed grafts were only long strips of graft can be utilized (4). Therefore is a preferable technique for especially extensive wounds (2). Graft failure due to bacterial infection is limited to failure of a few islands instead of the whole graft, because of all separate gauzes. Moreover, in our experience the scar quality of micrografts showed to be very good and might even better

than the scars of meshed grafts. Drawbacks of micrografting are mainly based on a more labour-intensive and time-consuming procedure compared with meshed grafts.

